## **1.0 Purpose of the study:**

This study aims to develop and refine a survey instrument that evaluates consumer perception of a healthy label and the willingness to pay for it. The overall objectives of the project are to:

1. Understand and describe behaviorally segmented elasticity measures and estimates of the response to variations in nutrition-related food labeling.
2. Evaluate the impact of trust in various food-related institutions on food choice.
3. Evaluate the impact of a “healthy” food label, both with and without FDA endorsement, on snack food choices.
4. Identify nutrition-related food label components best suited for policy and regulatory updates aimed at improving the healthfulness of snack food choices.

This project is divided into two Phases. The primary objective of Phase 1 of this project is to pre-test the survey tool to refine and improve the presented content. Data collected from Phase 1 will not be retained or used for further analysis beyond the improvement of the survey for Phase 2. Phase 2 will proceed only after protocol modifications are submitted to incorporate feedback from the pretesting done in Phase 1. The focus of this application is for approval for Phase 1.

### Phase 2 – Full Collection

Phase 2 includes the edits to the instrument after the feedback received from Phase 1 – Pretesting. The focus of this application is for approval for Phase 2.

## **2.0 Background / Literature Review / Rationale for the study:**

The U.S. Food and Drug Administration (FDA) announced in 2016 that it would begin redefining “healthy” food labels, in part spurred by a dispute with KIND Snacks about its use of the term on KIND Bar packaging. The lack of an updated regulatory definition of the term has left food companies like KIND vulnerable to class action and consumers vulnerable to confusing or misleading food labels. The FDA, however, has made no regulatory decisions since the initial 2016 request for information. In the interim, the FDA has held a public meeting on the redefinition, updated its Nutrition Innovation Strategy to include defining the term, and got approval from the Office of Management and Budget (OMB) to create a focus group review of a “healthy” icon on food packages. Most recently, OMB approved another proposal from the FDA to redefine the term and produce additional research on developing a “healthy” front-of-package (FOP) icon. However, no research evaluating the impact of a “healthy” label, particularly one endorsed by the FDA, currently exists in a U.S. population.

The influence of an FDA-endorsed “healthy” label on food choice is also presumed to interact with the level of trust participants have in food-related institutions like the FDA. Survey questions of attitude-based trust questions (e.g., “generally speaking, would you say that most people can be trusted or that you can’t be too careful in dealing with people?”) have shown varying relationships with choice.

The lack of trust in the food value chain is a significant problem analyzed in the literature (Hobbs and Goddard, 2015; Sapp et al., 2009; Kaiser and Algers, 2017). With increasing claims about product credence characteristics, the lack of trust most likely decreases consumer confidence in their ability to make informed food choices (De Jonge et al. 2007). Consumers need to trust that manufacturers and farmers do what they say they do and that the government enforces regulations regarding misleading claims. Research has examined consumer trust levels among farmers, retailers, manufacturers, and the government. For instance, Macready et al. (2020) found that consumers in five European countries had different opinions about which institutions to trust. Spanish consumers have a higher level of trust except for trust in the government. Meanwhile, French consumers have lower levels of trust, except trust in the government.

Previous literature has shown that real choice experiments (RCE) have a high level of external validity (Chang et al., 2009), and it reduces hypothetical bias (Lusk, J. and Schroeder, T.C., 2004). In hypothetical settings, individuals have little incentive to put cognitive effort into their decision. RCEs have been used before to study food labels for Organic products (Chen et al. 2019) and traceability (Wu et al. 2015). We are closing the literature gap by adding a novel label and comparing it with other labels.

We are using Real Choice Experiments, which are more realistic than hypothetical experiments and have been demonstrated to lead to higher external validity. Real choice experiments require real economic incentives. This strategy involves informing participants that one of the choice scenarios will be selected at random and will be binding in terms of purchasing. Hence, participants have to buy the chosen products in the binding scenario and pay the corresponding price. To implement an RCE, the product to be valued needs to have quality attributes that can be easily varied and are widely available on the market (Ballco and Gracia, 2020).

### **3.0 Participant Population:**

The pre-testing participants will be adults 18 years or older responsible for shopping for their household. Subjects will be recruited from the Greater Boston area. Participants will be English-speaking adults recruited at the specific locations listed below. No demographic quotas will be used to determine the target study sample demographics.

#### Phase 2 – Full Collection

The participant population is the same as pre-testing participants.

### **4.0 Special Populations:**

N/A

- ☐ Children
- ☐ Fetuses/Neonates
- ☐ Prisoners
- ☐ Members of the military
- ☐ Non-English speakers

- ☐ Those unable to read (illiterate)
- ☐ Employees of the researcher
- ☐ Students of the researcher
- ☐ Adults lacking capacity to consent and/or adults with diminished capacity to consent, including, but not limited to, those with acute medical conditions, psychiatric disorders, neurologic disorders, developmental disorders, and behavioral disorders
- ☐ Disadvantaged in the distribution of social goods and services such as income, housing, or healthcare
- ☐ Fear of negative consequences for not participating in the research (e.g., institutionalization, deportation, disclosure of stigmatizing behavior)
- ☐ Approached for participation in research during a stressful situation such as emergency room setting, childbirth (labor), etc.

## **5.0 Research Locations and Sample Size:**

### **5.1 Research Locations**

During pretesting, participants will be recruited from a variety of retail food establishments in the Boston area, including farmers' markets, grocery stores, and specialty food stores. The research will be conducted at a table located within the establishments' retail space. The first phase will include the Medford Farmer's Market, Stop & Shop and Daily Table.

#### Phase 2 – Full Collection

During full collection, participants will be recruited from a variety of retail food establishments in the Boston area, including farmers' markets, grocery stores, and specialty food stores. The research will be conducted at a table located within the establishments' retail space. The first phase will include Stop & Shop, Daily Table and the Big Y.

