#### Phase 2 – Full Collection

Participants will be provided with a total value of up to \$15.00. Up to \$5.00 will be used to purchase study products at the study site from one of the research team members. Participants will keep the change for this \$5.00. If the snack product is less than \$5, participants will be able to keep the change from the purchase. If for the selected binding choice scenario, the participant selected “no purchase”, the participant will be able to keep the \$5. An additional \$10.00 will be given to participants in the form of gift cards / vouchers from Stop & Shop, Daily Table or the Big Y, depending on where testing takes place. Vouchers / gift cards will be handed to the participant by a research team member once the survey has been completed.

Participants will be made aware of the compensation amount before beginning the survey. After completing the survey, they will be provided the chosen study product and remaining monetary compensation. Participants will only receive compensation if they complete the experimental portion of the survey.

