## Analysis Plan

### Statistical Models

We will run the following models to test our hypothesis.

- A binary logistic regression to assess the proportion of participants that choose healthy and unhealthy snack choices. The main predictor variable is the presence of an FDA Healthy, Healthy, or Food Compass Score. Other predictor variables to analyze are generalized trust, personal trust, institutional trust and trust in the government, knowledge, physical activity levels, diet, and sociodemographics.

We will run the same model for each treatment to test, for example, hypothesis H2.

- We plan to run a multinomial logit model (MNL), random parameter model (RPL), random parameter model with EC (RPL-EC), and latent class analysis (LCA) to investigate participants' willingness to pay on each treatment. We will use the presence of a healthy label or food compass score, and price as the main attributes of the utility function for the MNL, RPL, RPL-EC and LCA. However, for the LCA we will use generalized trust, personal trust, and trust in the government (according to hypothesis H2) as consumers' characteristics for the segment membership function.

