### Transformations

We will use simple coding for the following categorical variables:

- Income
- Education
- Race

The variable "Diet" will be a dummy variable that takes the value of 0 if participants responded no / not applicable, and the value of 1 if any of the other options is selected.

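### No Phase 2 model includes store, so trust coefficients may be confounded by store clientele, as may label contrasts if treatments are between participants and uneven across stores

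*Combined protocol and SAP*

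**What the plan says.** **Recruitment.** The Phase 2 text of Section 5.1 says that "participants will be recruited from a variety of retail food establishments in the Boston area", covering farmers' markets, grocery stores and specialty shops. It then states: "The first phase will include Stop & Shop, Daily Table and the Big Y". The list is open-ended and branches are not specified. Section 3.0 says: "No demographic quotas will be used to determine the target study sample demographics". Its Phase 2 paragraph keeps the same population. Under Section 9.0, shoppers are invited at a study table while they shop.

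**Whether store is known.** Section 11.0 (Phase 2) has the voucher issued by one of the named stores, "depending on where testing takes place". Staff therefore know the site. No section defines a store variable or says that site is attached to the survey response.

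**Models.** For the logistic regression the Analysis Plan (Statistical Models) says: "Other predictor variables to analyze are generalized trust, personal trust, institutional trust and trust in the government, knowledge, physical activity levels, diet, and sociodemographics". For the choice models it says: "We will use the presence of a healthy label or food compass score, and price as the main attributes of the utility function". On segment membership it says that "for the LCA we will use generalized trust, personal trust, and trust in the government". Under Transformations, "We will use simple coding for the following categorical variables" introduces income, education and race. Inference Criteria adds paired t-tests and ANOVA between treatments and names no covariates.

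**Treatments.** Neither the protocol nor the Analysis Plan says how treatments are assigned to participants or spread over stores. Data Exclusion checks that each participant completed the scenarios for all three treatments, which can be read as every participant receiving all three.

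**The concern.** Different stores may attract different shoppers. If shoppers at one store are both more trusting and more inclined to healthy snacks, for reasons other than the covariates in the model, a model without store attributes part of that difference to trust.

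Treatment allocation gives no protection here. Trust varies only between people, and the same logistic model is fitted for each treatment, so every trust coefficient is a comparison between people. Objective 2 in Section 1.0, the effect of institutional trust on food choice, rests on these coefficients. The exploratory plan replaces one trust index with another when the first does not predict, and the replacement has the same exposure.

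The label comparisons are at risk only under a further condition. If each participant receives one treatment, and some treatments are run more at some stores, the contrast between treatments includes a contrast between stores.

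**Working it through.** **1. Reading each specification.**

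| Analysis | Terms listed | Store? |
|---|---|---|
| Logistic models | Label or score, trust indices, knowledge, activity, diet, sociodemographics | No |
| MNL, RPL, RPL-EC, LCA utility | Label or score, and price, as main attributes | No |
| LCA membership | Three trust indices | No |
| Paired t-tests, ANOVA | None stated | No |

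The logistic models adjust for some clientele differences. The membership function and the tests list no such adjustment.

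**2. Inputs for a size check.** The plan gives 350–400 participants, justified by saturation of feedback. It gives no power, effect size or standard deviation, so there is no planned figure to reproduce. From the documents: N = 400, 8 choices per person (Section 6.0, Phase 2) and the 0.05 level, taken here as two-sided. The same Section 6.0 text also says nine choices and the Analysis Plan says twelve; these need reconciling. The false-positive rates below depend on this number; the bias formula does not. Assumed: three equally likely stores, person-level random effect with SD 0.7 on the logit scale, two treatments compared, and the store differences shown. True trust and treatment effects are zero. Each simulated scenario has 600 replicates, fitted as a binomial model with robust standard errors.

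**3. Trust bias by formula.** Code the stores c = −1, 0, +1, so Var(c) = 2/3. Let mean trust rise by d SD and healthy choice by s logits per store step. With store omitted:

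bias ≈ s × d·V / (1 + d²·V), with V = 2/3.

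For d = 0.25 and s = 0.5: 0.5 × 0.1667 / 1.0417 = 0.080.

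If the model also holds a covariate that differs by 1 SD per store step, V falls to 2/3 − (2/3)² / (2/3 + 1) = 2/5. The same case gives 0.5 × 0.100 / 1.025 = 0.049.

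**4. Trust, formula and simulation, store omitted.** FP is the false-positive rate. The last three columns are with the store-related covariate.

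| d (SD) | s (logit) | Formula | Simulated bias | FP | Formula | Simulated bias | FP |
|---|---|---|---|---|---|---|---|
| 0.1 | 0.2 | 0.013 | 0.015 | 6.5% | 0.008 | 0.005 | 4.0% |
| 0.25 | 0.25 | 0.040 | 0.034 | 11.5% | 0.024 | 0.022 | 6.2% |
| 0.25 | 0.5 | 0.080 | 0.070 | 32% | 0.049 | 0.046 | 16% |
| 0.5 | 0.5 | 0.143 | 0.128 | 81% | 0.091 | 0.084 | 45% |

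The simulated values are mostly a little lower because averaging over the person effect shrinks logit coefficients. If trust does not differ by store (d = 0, s = 0.5), bias is about 0 and rejection about 6%. For scale, a 0.5 logit step around 50% means healthy-choice rates near 38%, 50% and 62%, since 1/(1 + e^0.5) = 0.378.

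**5. Label contrast, between participants, store omitted, s = 0.5.** The columns give the share on one treatment at the three stores.

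| Shares | Simulated bias (logit) | FP |
|---|---|---|
| 50/50/50% | about 0 | 5% |
| 40/50/60% | 0.12 | 25% |
| 25/50/75% | 0.30 | 88% |
| 0/50/100% | 0.60 | 100% |

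On the percentage scale, assume healthy-choice rates of 40%, 50% and 60% by store. Store mixes of 30/30/40 and 40/30/30 give 0.12 + 0.15 + 0.24 = 51% and 0.16 + 0.15 + 0.18 = 49%, a spurious 2 points. Mixes of 20/30/50 and 50/30/20 give 53% and 47%, a spurious 6 points. If every participant receives all three treatments, store cancels from the within-person contrasts.

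**6. With store indicators added.** Mean bias for trust and for treatment was at most about 0.01 logit, and rejection was about 4–8% in every scenario (Monte Carlo standard error about 1 point).

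**The case against.** The best defence is that the logistic models already include knowledge, activity, diet and sociodemographics, which are the obvious ways in which store clienteles differ. Only a residual association of store with both trust and healthy choice can bias the trust coefficient. This stands. In the simulation one store-related covariate cut the false-positive rate from 32% to 16% and from 81% to 45%, and small store differences were harmless even without it. It does not help the membership function, which lists trust only.

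A second objection is over-adjustment: if trust influences where people shop, conditioning on store may remove part of the effect of interest. That is possible, though the documents do not bear on it. Reporting the trust results with and without store deals with it.

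Third, the label half may not arise, since Data Exclusion can be read as a within-participant design and paired tests are planned. This also stands, and that half is conditional here.

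Three stronger readings are tempting and unsupported:
- A reader might infer that the trust effects are in fact confounded. The documents contain no data on trust or choice by store.
- A reader might infer from the voucher rule that store is already in the dataset. The rule shows only that staff know the site.
- A reader might treat the store-specific voucher as a further source of bias. Its value is \$10 at every store and it is handed over after the survey, so it adds little.

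**Conclusion.** The omission is real: Phase 2 recruits by convenience at several stores, and store enters no planned model or test. The conclusion it supports is that trust coefficients may be confounded, with the greatest exposure in the latent class membership function. Label contrasts may be biased only if treatments are between participants and uneven across stores.

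The size cannot be established from the documents. Under assumed differences the bias in the trust coefficient ran from about 0.01 to 0.13 logit, so negligible and serious outcomes are both possible. Those figures come from the logistic form with three equal stores; the latent class model was not simulated. The plan states no detectable effect against which to compare them. The case for the change is its low cost and that store must be captured at the time of collection.

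**What to change.** - Add a store field to each survey response, entered by staff.
- Add store indicators to the logistic models and to the LCA membership function. With about three stores, fixed indicators are preferable to a random effect.
- Report the trust results with and without store.
- State how treatments are assigned, and report treatment-by-store counts. If treatments are between participants, take the treatment comparison from a store-adjusted model, not from the unadjusted ANOVA.

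The cost is one survey field, plan wording and a few degrees of freedom: the number of stores minus 1 in each logistic model (2 with three stores), and the same number per non-reference class in the membership function. With 350–400 participants this is small. The remaining downside is slight over-adjustment if trust influences store choice, which the paired reporting would help to show.

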### **5.2 Sample Size**

The expected sample size for pre-testing our survey instrument in Phase 1 is up to 100 participants; we expect to reach saturation on feedback and error detection with 50-100 participants.

#### Phase 2 – Full Collection

The expected sample size for full collection is up to 400 participants; we expect to reach saturation on feedback and error detection with 350 - 400 participants.

## **6.0 Procedures Involved:**

### Design

Qualtrics is used to host a survey to evaluate consumers' perceptions and willingness to pay for a healthy label consisting of a Real Choice Experiment with additional sociodemographic and attitudinal questions. Question types include single choice, multiple choice, Likert scale, and open-answer questions.

### Pre-Testing

The first phase of this study involves pre-testing the Qualtrics survey in the summer of 2022. A table will be set up for willing market shoppers to stop and take the survey on iPads provided by Tufts. At the end of the survey, they will be asked for feedback about the survey (see the attached semi-structured interview script). The survey is expected to take 20-25 minutes to complete.

As part of the choice experiment section, participants will be presented with choices between two to three snack food products and accompanying renderings of food labels for each product. Participants select only one product on each choice scenario (they will be exposed to 9 choice scenarios). Alternatively, if participants don't want to choose any of the snack products, they can opt out by choosing the "no purchase" option. After they finish making their nine choices, they will randomly pick a number to select one of the nine choice scenarios as the binding choice scenario. Participants will only pay for the (one) snack product they chose in the binding choice scenario. If the participant selected the "no purchase" option in the selected binding choice scenario, they won't receive a product and won't have to pay anything. The research team will have the snack products readily available so participants can have their product as soon as they pay for it.

Since the Real Choice Experiment mandates that the selection is binding and that the subject will pay for their chosen product, the research team will give participants \$5 cash at the beginning of the study after they signed the consent form and answer the screening questions. The screening questions are if participants are 18 years or older and if they are responsible for shopping for food for the household.

### Phase 2 – Full Collection

The second phase of this study involves full collection of the experiment using our survey on Qualtrics in the Winter / Spring of 2023. A table will be set up for willing market shoppers to stop and take the survey on iPads provided by Tufts. The survey is expected to take 15-20 minutes to complete.

As part of the choice experiment section, participants will be presented with choices between two to three snack food products and accompanying renderings of food labels for each product. Participants select only one product on each choice scenario (they will be exposed to 8 choice scenarios). Alternatively, if participants don't want to choose any of the snack products, they can opt out by choosing the "no purchase" option. After they finish making their nine choices, they will randomly pick a number to select one of the nine choice scenarios as the binding choice scenario. Participants will only pay for the (one) snack product they chose in the binding choice scenario. If the participant selected the "no purchase" option in the selected binding choice scenario, they won't receive a product and won't have to pay anything. The research team will have the snack products readily available so participants can have their product as soon as they pay for it.

Since the Real Choice Experiment mandates that the selection is binding and that the subject will pay for their chosen product, the research team will give participants \$5 cash at the beginning of the study after they signed the consent form and answer the screening questions. The screening questions are if participants are 18 years or older and if they are responsible for shopping for food for the household.

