### Data Exclusion

We will verify that each participant answered each of the twelve choice scenarios for the three treatments. Straightlining: If found that participant will be excluded from the survey. Outliers will be included in the analysis.

47  
48 **Missing Data**  
49

50 If a participant doesn't answer any of the twelve choice scenarios, and / or answer the trust-related  
51 questions, that participant will not be included in the analysis.  
52

53 **Exploratory Analysis**  
54

55 If the institutional trust index doesn't predict the probability of choosing a healthy snack labeled with a  
56 Food Compass Score, we will explore the effect of interpersonal trust or generalized trust in the logistic  
57 regression.  
58

59 If the index measuring trust in the government doesn't predict the probability of choosing an FDA-  
60 healthy snack, we will explore the effect of interpersonal trust or institutional trust in the logistic  
61 regression.

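### The Phase 2 procedure and the analysis plan give 8, nine and twelve choice scenarios per participant; the counts cannot all hold, and both the binding draw and the completeness rule depend on them.

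*Combined protocol and SAP*

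**What the plan says.** Section 6.0 (Procedures Involved), under Phase 2 – Full Collection, contains two counts. On what is shown: "they will be exposed to 8 choice scenarios". On what follows, in the same paragraph: "After they finish making their nine choices, they will randomly pick a number to select one of the nine choice scenarios". The scenario drawn is the binding one, which fixes what the participant buys, if anything.

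The Pre-Testing text for Phase 1 in the same section uses nine throughout: "they will be exposed to 9 choice scenarios". Its sentence on the nine choices and the draw is the same as the one in the Phase 2 text.

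The Analysis Plan has a third count. Under Data Exclusion: "We will verify that each participant answered each of the twelve choice scenarios for the three treatments". Under Missing Data, the rule that removes participants from the analysis begins "If a participant doesn't answer any of the twelve choice scenarios" and adds a condition on the trust questions.

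The Analysis Plan names no phase. Section 1.0 says that Phase 1 data serve only to improve the survey, so the plan can only govern Phase 2.

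**The concern.** The number of scenarios per participant does two jobs in this study.

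First, it sets the range of the random draw. Section 2.0 rests the case for a real choice experiment on one randomly selected scenario being binding in money. Under section 11.0 the same draw determines whether the participant buys a product and how much of the $5 is kept. A draw over more scenarios than were shown can select one for which no choice exists.

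Second, it defines a complete participant. A completeness standard of twelve cannot be met in a survey of 8 or nine. Whoever prepares the analysis set would have to replace a prespecified rule with one of their own. If that happened after the data had been examined, the exclusions would no longer be prespecified.

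**Working it through.** The documents contain no sample-size, power or precision calculation that uses the scenario count, so there is no planned figure to reproduce. The check compares the counts and follows each through the rules as written.

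**Inputs**
- Scenarios shown, Phase 2: 8 (section 6.0, Phase 2)
- Choices made and range of the draw, Phase 2: 9 (same paragraph)
- Scenarios in the completeness check and missing-data rule: 12, for three treatments (Analysis Plan, Data Exclusion and Missing Data)
- Participants, Phase 2: 350 to 400 (section 5.2)

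**Step 1: the binding draw, if 8 are shown and the draw is uniform over nine**
- P(the number drawn has no scenario behind it) = (9 − 8)/9 = 1/9 = 11.1%.
- Expected number of such draws: 350/9 = 38.9, about 39; 400/9 = 44.4, about 44.
- P(at least one in the study), with independent draws = 1 − (8/9)^N, which exceeds 0.999 at both N = 350 and N = 400.

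**Step 2: the completeness check against twelve**
- If 8 are shown, at most 8/12 = 67% of the required scenarios can be answered.
- If nine are shown, at most 9/12 = 75%.
- In either case 0 of 350 to 400 participants can have answered all twelve. If twelve were meant per treatment (12 × 3 = 36), the gap would be wider.

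**Step 3: what happens under each possible true count, with the other text left as written**

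| Scenarios really shown | Draw over nine | Check against twelve |
|---|---|---|
| 8 | 1/9 of draws have no scenario behind them | cannot be met |
| 9 | sound | cannot be met |
| 12 | 12 − 9 = 3 scenarios can never be binding | can be met |

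Under none of the three counts do both the draw and the check work as written.

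**Step 4: what the missing-data rule does**

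The rule can be read in two ways.
- *Fails to answer any one of the twelve.* With 8 or nine shown, every participant meets this condition and is excluded.
- *Answers none of the twelve.* A participant who answered all 8 is kept, but so is one who answered a single scenario.

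The text does not settle which is meant. The first reading fits better with the Data Exclusion sentence, which looks for an answer to every scenario.

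**Step 5: search for a reconciling statement**

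No section mentions practice tasks, blocks, repeated tasks or a per-treatment count that would connect 8, nine and twelve. Section 18.0 requires the choice tasks to be answered for a complete response but gives no number.

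**The case against.** The strongest reply is that this is leftover wording with no practical effect. The nine in the Phase 2 text matches the Phase 1 sentence, so the draw in use may already run over 8. A draw with no scenario behind it would be noticed at the table, where a team member is present. A redraw would leave each of the 8 real scenarios with probability (1/9)/(8/9) = 1/8, so the incentive would remain fair. In the Analysis Plan, the verification sentence states no consequence, and the missing-data rule can be read as removing only those who answered nothing. Section 18.0 supplies a completeness requirement that works with any count.

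Much of this stands. It makes the 1/9 figure and the total exclusion conditional, and the incentive design as a whole is not shown to fail. But no redraw rule is written down, and no reading brings 8, nine and twelve into agreement.

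A reader might infer three further things, which the documents do not support:

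- **A shortfall in data.** At 400 participants, 8 scenarios give 3,200 choices and twelve give 4,800, which looks like a one-third loss. But twelve appears only in the exclusion and missing-data rules. No power calculation or target number of choices rests on it.
- **An error because 8 does not divide by three.** No section requires an equal split over treatments. An uneven split is possible; it is simply not described.
- **A certain loss of all participants.** The team would probably apply the rule to the scenarios actually shown. What can be said is that the rule is unworkable as written.

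**Conclusion.** The point holds as an internal contradiction with conditional consequences. Section 6.0 for Phase 2 gives two counts (8 and nine) and the Analysis Plan a third (twelve). The plan's link to Phase 2 is an inference from section 1.0, but a secure one.

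The size depends on which count is true, and the documents do not show that:
- Invalid draws at a rate of 11.1% (about 39 of 350 or 44 of 400) require both that 8 are shown and that the draw is run over nine. If nine are shown, no draw is invalid.
- The impossibility of meeting the twelve-scenario check requires only that 8 or nine are shown.
- Exclusion of every participant requires, in addition, the reading of the missing-data rule as failing to answer any one of the twelve.

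This is more than a typing slip, because the count fixes both the range of the incentive draw and the stated condition for entering the analysis. It needs correcting, and the correction is cheap.

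**What to change.** 1. State one scenario count, K, equal to the number actually programmed for Phase 2.
2. In section 6.0, Phase 2, make the number shown, the number of choices made and the range of the binding draw all equal to K.
3. In the Analysis Plan, replace twelve with K under both Data Exclusion and Missing Data, and state how the K scenarios map to the three treatments.
4. Reword the missing-data rule so that it can be read in only one way. If the intention is to exclude participants who leave one or more of the K scenarios unanswered, say exactly that.
5. Make these changes before the data are examined, so that the exclusion rule remains prespecified.

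The cost is wording edits in two places and a check of the count against the programmed survey. A hand draw from 1 to K is sufficient; no change in how the number is drawn is needed. No additional participants are required.
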